## Aims and objectives

Within the InAdvance project at four locations a randomized trial will be performed lasting 18 months after the first intervention. In Valencia (Spain), Amadora (Portugal), Thessaloniki (Greece) and Highlands (UK) a novel model of palliative care will be implemented by integrating personalized pathways for palliative care that starts at an early stage of complex chronic conditions for older people (≥60 years old). The objective of our study is to evaluate acceptability, feasibility, effectiveness and cost-effectiveness of the novel model of palliative care in patients with chronic conditions.

In terms of effectiveness, self-reported outcome measures will be assessed with regard to both patients and informal caregivers/relatives to analyze the impact of the intervention on their wellbeing. The cost-effectiveness evaluation will assess whether there is ‘value for money’ and cost savings derived from the intervention. Finally, the implementation of the interventions process will be assessed at several times with the involvement of key healthcare professionals to identify facilitators and barriers of the implementation of the interventions.

We hypothesize that patients will have improved or maintained HRQoL and alleviated symptoms, and that multifaceted, complex needs including psychological, emotional and spiritual needs will be addressed. Informal caregivers/relatives will have improved or maintained HRQoL, increased social support, caring and coping skills and decreased caregiving burden. From the cost-effectiveness evaluation, we hypothesize that patients will have more efficient use of health care resources and contribute to a reduction of unnecessary costs.

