### Data management and statistical analysis

The University of Valencia (UVEG) and the Erasmus Medical Center (Erasmus MC) are responsible for the analysis and reporting. UVEG, Erasmus MC and together with all clinical sites are responsible for the data manegement. All data will be gathered through the CASTOR eCRF system, which will be made available to the consortium.

Descriptive statistics will be carried out to summarize characteristics of participants in each clinical site and in the total study population. Tests for normal distribution of the continuous outcome measures will be performed using the Kolmogorov–Smirnov test. The outcome measures will be compared within each group (intervention group and control group) at different measurement times (i.e. T0-T1; T1-T2; T2-T3; T3-T4; T1-T4; T0-T4, etc.). A multilevel modelling approach will be used to examine differences in the outcome measures between the intervention and control group, taking into account the clustering effects at the clinical site level. The relationship between the outcome measures and independent variables will be assessed using Pearson correlation (for continuous variables) and Pearson Chi-square test (for categorical variables). Comparison between the intervention group and the control group at each evaluation moment will be conducted by including an interaction between the treatment groups and time in the multilevel model.

The cost-effectiveness analysis will be conducted from a societal perspective and on a within-trial horizon. The incremental cost-effectiveness ratio (ICER) will be calculated and the degree of uncertainty for costs and effectiveness and the cost-effectiveness ratio will be examined on the ICER by using non parametric bootstrapping. In addition, an acceptability curve will be generated to indicate the probability that the intervention has lower incremental costs per quality adjusted life year (QALY) gained than various thresholds for the maximum willingness to pay for an extra QALY.

In all cases, *p*-values < 0.05 will be considered statistically significant. All analyses will be carried out using the statistical package SPSS v26 or similar statistic software packages.

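### The acceptability curve is defined by setting a ratio against the threshold, which is not the probability of cost-effectiveness once bootstrap replicates span quadrants

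*Protocol article*

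**What the plan says.** Under *Data management and statistical analysis*, the protocol article plans an economic evaluation "conducted from a societal perspective and on a within-trial horizon". The summary measure is a ratio: "The incremental cost-effectiveness ratio (ICER) will be calculated". Uncertainty in costs, in effectiveness and in that ratio is then "examined on the ICER by using non parametric bootstrapping". An acceptability curve is added, and its meaning is spelled out: it gives "the probability that the intervention has lower incremental costs per quality adjusted life year (QALY) gained than various thresholds". The thresholds themselves are left open: "various thresholds for the maximum willingness to pay for an extra QALY". The section does not mention net benefit, quadrants of the cost-effectiveness plane or dominance.

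Under *Aims and objectives*, the hypotheses are that "patients will have improved or maintained HRQoL and alleviated symptoms" and, on the economic side, that the intervention will "contribute to a reduction of unnecessary costs".

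**The concern.** An acceptability curve should give, at each threshold, the probability that the intervention is worth its cost. The article describes it instead as the probability that a ratio lies below the threshold. A ratio does not change when both its signs flip. A replicate with higher cost and fewer QALYs has a negative ratio and so lies below every positive threshold, although it is the worst possible result. A replicate with savings and a QALY loss is acceptable only when its ratio is *above* the threshold, which is the reverse of the stated rule.

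Reading the definition as covering only replicates with a QALY gain removes the first fault but creates another. A replicate with large savings and a trivial QALY loss can then never count as cost-effective.

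This matters because cost-effectiveness is a named objective and the results are meant to inform policy recommendations and clinical guidelines. If quality of life is maintained and costs fall, many replicates will lie near zero QALY difference or in the lower-cost, fewer-QALY quadrant. That is where the stated definition fails on both readings.

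**Working it through.** **Inputs.** From the documents: the definition of the curve, the use of bootstrap replicates, and the hypothesised directions of effect and cost. The documents state no probability, cost, QALY variance or threshold, so there is no figure to reproduce. Assumed for illustration: incremental QALY (E) and incremental cost (C) independent and normal, standard errors 0.03 QALY and 1,200 cost units, threshold λ = 20,000.

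**Decomposition.** Split the replicates as follows:
- A = P(E > 0 and C < λE): a QALY gain at acceptable cost.
- S = P(E < 0 and C < λE): a QALY loss outweighed by savings.
- B = P(E < 0 and C > λE): a QALY loss not outweighed by savings. This includes every replicate with higher cost and fewer QALYs.

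The three rules are then:
- Net benefit, P(λE − C > 0) = A + S.
- Plain ratio, P(C/E < λ) = A + B.
- Gains only, P(E > 0 and C/E < λ) = A.

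The plain ratio is therefore wrong by B − S, and the gains-only count is always too low, by S. Since B + S = P(E < 0), neither error can exceed the share of replicates with a QALY loss.

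**No true effect.** λ × 0.03 = 600, so A = 1/4 + arctan(600/1,200)/(2π) = 0.250 + 0.074 = 0.324. By symmetry B = 0.324 and S = 0.500 − 0.324 = 0.176. Plain ratio: 0.648. Gains only: 0.324. Net benefit: 0.500.

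**No QALY difference, 1,000 saved.** Net benefit = Φ(1,000/√(1,200² + 600²)) = Φ(1,000/1,341.6) = Φ(0.745) = 0.772. Numerical integration gives A = 0.441, B = 0.169, S = 0.331. Plain ratio: 0.441 + 0.169 = 0.61 after rounding. Gains only: 0.44.

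**All scenarios, same assumptions:**

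| True difference (QALY, cost) | Plain ratio | Gains only | Net benefit |
|---|---|---|---|
| 0, 0 | 65% | 32% | 50% |
| 0, −1,000 | 61% | 44% | 77% |
| −0.01, +500 (worse on both) | 68% | 17% | 30% |
| +0.01, −500 (better on both) | 68% | 50% | 70% |
| +0.06, +500 | 71% | 69% | 70% |
| +0.06, 0 | 82% | 80% | 81% |
| +0.06, −1,000 | 94% | 93% | 95% |

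The third and fourth rows are mirror images. The plain ratio gives both the same 68%; net benefit separates them at 30% and 70%. In the last three rows the QALY gain is two standard errors, only 2.3% of replicates show a loss, and the largest gap is 1.7 points.

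**Sensitivity.** With a cost standard error of 1,000 and λ = 30,000, the plain, gains-only and net-benefit figures are 73/37/50% for no effect, 62/34/70% for 1,000 saved with a 0.01 QALY loss, and 85/83/83% for +0.06 QALY at +500. With no effect, the plain figure runs 67%, 73% and 81% at λ = 20,000, 30,000 and 50,000, while net benefit stays at 50%.

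**The case against.** The strongest reply is that this is a familiar verbal short form in a condensed article. The rule for classifying replicates may sit in a full protocol or analysis plan that is not shown, and nothing in the text prevents the analysts from using net benefit. Part of this stands: the team may well compute the curve correctly. But the article does not leave the definition out. It gives one, and that definition yields the intended probability on neither literal reading.

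Three stronger inferences are tempting, and the documents do not support them.
- *That the plan counts dominated results as cost-effective.* The text does not say so. Because it speaks of a QALY gained, its literal wording can be read as excluding them. That reading fails in the opposite direction, by dropping worthwhile savings.
- *That the analysis could not tell which arm is better.* This is true of a plain-ratio curve taken alone. The plan also bootstraps costs and effectiveness, and that would show the sign of each difference.
- *That a misleading percentile interval for the ratio is planned.* No such interval is mentioned.

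The size can also be contested, because the hypothesis includes improved as well as maintained quality of life. If the planning effect of 0.20 applied to QALYs with 160 per arm (an assumption), the mean gain would be 0.20 × √(160/2) = 1.79 standard errors. About 4% of replicates would then show a loss, and under the assumptions above no gap exceeds 3 points for cost differences from −1,000 to +500. This stands: the error is large only when a material share of replicates shows a QALY loss.

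**Conclusion.** The point holds as a fault in the stated definition, not as a demonstrated error in an analysis. Applied literally, the definition does not give the probability of cost-effectiveness once replicates span quadrants. The plain-ratio reading can err in either direction, and the gains-only reading is always too low.

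Under the assumed standard errors and threshold, the error is 15 to 18 points with no effect and 16 to 33 points with maintained QALYs and 1,000 saved. It is about 2 points or less when the QALY gain is two standard errors. These sizes rest on assumed variances, independence and normality. The decomposition and the direction of the gains-only error do not. The large-error scenarios are plausible because the trial's own hypotheses allow maintained quality of life with lower costs.

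**What to change.** Replace the definition with this: at each threshold, the curve shows the share of bootstrap replicates in which threshold × incremental QALY − incremental cost is greater than zero, that is, the probability that incremental net monetary benefit is positive. Alongside the ICER, show the replicates on the cost-effectiveness plane, so that readers can see how many fall in each quadrant.

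This changes one sentence and adds one plot. It uses the same bootstrap output and needs no further data. There is no downside: where nearly all replicates show a QALY gain, the result is almost unchanged.

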### Sample size considerations

Assuming a statistical power of 95% and an effect size of 0.20 regarding continuous outcome measures between intervention and control group with an alpha risk of 0.05, the sample size is estimated to be 320 participants; that is 80 at each of the four sites with 40 participants in the intervention group and 40 in the control group. In the study, for each patient participating in the study, it is expected to include one informal caregiver (e.g. a family member) who provides informed consent to join the study. Furthermore, for the formative evaluation, 10–15 health care professionals will be recruited to participate in the study at each study site.

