### Outcome measures and data collection

Data will be collected using self-reported questionnaires translated into the official language of each country. Validated translations will be used. When needed, the questionnaire will be translated with the forward-backward translation technique [30] and tested in each setting after being reviewed and adapted. Before the start of the study, questionnaires will be pilot-tested in all participating. The instruments used to measure the outcomes are described below.

Patient-reported outcomes to evaluate trial effectiveness includes HRQoL, intensity of symptoms, functional status, emotional distress, perceived quality of care and adherence to treatment. HRQoL is measured with the EQ-5D-5L instrument [31], which includes: mobility, self-care, usual activities, pain/discomfort and anxiety/depression. Intensity of symptoms is measured with the Palliative Care Outcome Scale (POS) [32]. The POS measures patients’ physical, psychological, emotional and spiritual symptoms, and is suitable for use in both specialist palliative care and non-specialist palliative care settings. Functional status is measured via the Palliative Performance Scale Version 2 (PPSv2) that includes five domains: ambulation, activity & evidence of disease, self-care, intake and conscious level [33]. Emotional distress is assessed with the Hospital Anxiety and Depression Scale (HADS) among patients [34]. It is a two-dimension scale developed to identify depression and anxiety among physically ill patients and the general population valid at hospital and in community settings. Perceived quality of care is assessed through a 5-point Likert scale related to communication, information provided, personalized care, family-centred and overall satisfaction. Adherence to treatment is assessed through the Medical Outcomes Study (MOS) [35].

Emotional distress and perceived quality of care will also be assessed among relatives or informal caregivers. In addition, caregiving burden will be measured among relatives or informal caregivers through the brief version of Zarit Burden Interview (ZBI) [36]. ZBI aims to evaluate the perceived impact of providing care on aspects such as the caregiver’s health, personal and social life, financial situation, emotional wellbeing and interpersonal relationships [37, 38].

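### A flat p < 0.05 rule covers ten outcomes at four follow-up times with no primary endpoint, so the trial's false-positive rate is far above 5%

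*Protocol article*

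**What the plan says.** All references are to the protocol article.

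- **Significance rule** (Data management and statistical analysis). The section closes by stating, for all cases, that p-"values < 0.05 will be considered statistically significant". It gives no hierarchy, adjustment or exploratory label.
- **Between-arm tests** (same section). "Comparison between the intervention group and the control group at each evaluation moment" is obtained from a group-by-time interaction in a multilevel model. The section also plans comparisons within each arm over six named pairs of times, and leaves that list open.
- **Patient outcomes** (Outcome measures and data collection). "Patient-reported outcomes to evaluate trial effectiveness includes HRQoL, intensity of symptoms, functional status, emotional distress, perceived quality of care and adherence to treatment". That makes six.
- **Caregiver outcomes** (same section and Table 3). "Emotional distress and perceived quality of care will also be assessed among relatives or informal caregivers". Caregiver burden is added in the text and caregiver EQ-5D-5L in Table 3. That makes four.
- **Times** (Study design and Table 3). All ten outcomes are measured at T1, T2, T3 and T4.
- **Sample size** (Sample size considerations). The section opens with "Assuming a statistical power of 95% and an effect size of 0.20 regarding continuous outcome measures". From these inputs and an alpha of 0.05 it arrives at a total of 320, or 160 per arm. No particular outcome or visit is attached to this statement.

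The abstract, the aims, the outcome section, Table 3 and the analysis section do not name a primary outcome or a primary time point.

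**The concern.** A significance level of 0.05 describes the false-positive risk of one test. Here it is given to every test, and nothing says which of them answers the effectiveness question. The plan therefore does not control the chance that a trial of an ineffective intervention reports some significant difference between the arms. The 95% power and the alpha of 0.05 in the sample size belong to no identified comparison.

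The abstract says the results should inform policy recommendations and clinical guidelines. A reader of the eventual report could not tell whether one significant result, on one outcome at one visit, was the planned test or one of many.

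**Working it through.** **1. The plan's own figure.** For two equal arms, n per arm = 2(1.960 + 1.645)² / d² = 25.99 / d², with two-sided alpha 0.05 and 95% power.

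- Effect size 0.20 read as Cohen's f (d = 0.40): 25.99 / 0.16 = 162.4, so 163 per arm and 326 in total. This is close to the stated 320. Power with 160 per arm is about 95%.
- Effect size 0.20 read as a standardised mean difference: 25.99 / 0.04 = 649.7, so 650 per arm and 1,300 in total. Power with 160 per arm is about 43%.

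The stated total thus fits a single two-sided test at 0.05 under the first reading. The metric is not stated and should be, but that is a separate matter. What counts here is that the calculation allows for one test and does not say which.

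**2. Number of tests.** (6 patient + 4 caregiver outcomes) × 4 follow-up times = 40 between-arm comparisons. Costs, implementation measures and within-arm comparisons are left out.

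**3. Independent tests, no true effect on any outcome.**

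- Expected false positives: 40 × 0.05 = 2.
- At least one, either direction: 1 − 0.95^40 = 87.1%.
- At least one favouring the intervention (0.025 per test): 1 − 0.975^40 = 63.7%.

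**4. Correlated tests.** The article gives no correlations, so these are assumptions. Test statistics were simulated as multivariate normal, with one common correlation between outcomes and one between times (100,000 or more draws per setting).

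| Correlation between outcomes / times | 40 tests, either direction | 40 tests, benefit only |
|---|---|---|
| 0 / 0 | 87% | 64% |
| 0.3 / 0.5 | 76% | 44% |
| 0.5 / 0.6 | 64% | 34% |
| 0.5 / 0.7 | 60% | 31% |
| 0.7 / 0.8 (extreme) | 42% | 21% |

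**5. One overall test per outcome (10 tests).** Under independence, 1 − 0.95^10 = 40.1% in either direction and 1 − 0.975^10 = 22.4% for benefit. With a correlation of 0.5 between outcomes, these fall to about 29% and 14%.

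**6. Within-arm comparisons.** Two of the ten outcomes (patient adherence and caregiver quality of care) have no baseline measurement, so they lose the two named pairs that start at T0. The intervention arm then has 8 × 6 + 2 × 4 = 56 comparisons. Adding them to the 40 raises the chance of at least one falsely favourable result to 62–86%. This assumes correlations of 0–0.7 between outcomes within the patient and caregiver groups, 0–0.5 across those groups, and 0.5 or 0.7 between times. It also assumes no true change over time, which is doubtful in progressive disease, so this figure is only illustrative.

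**7. Benchmark.** One named outcome with one named contrast gives 5% two-sided, or 2.5% for a false benefit.

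**The case against.** The strongest case on the other side has four parts.

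- **The article is condensed.** The full protocol and analysis plan are not shown, and an outcome hierarchy or multiplicity rule may be set there. This stands as far as it goes: silence on adjustment would not be a fault. But the article is not silent. It fixes 0.05 for all cases, and an analysis plan that reserved 0.05 for one endpoint would contradict that sentence. Nor can one conclude that results will be picked after the fact, since that would assume the unseen documents contain nothing on the point.
- **Forty is one way of counting.** The visit comparisons sit inside one multilevel model per outcome, so ten overall tests is a fair lower count. This stands and is why step 5 is shown. Even then the risk in either direction is about 29–40%.
- **A significant difference is not a claim of effectiveness.** A reader might infer from the 87% or the 60–76% that a false claim of effectiveness is more likely than not. The documents do not support that. Those figures include differences against the intervention, and the article states no rule for turning a significant p-value into an effectiveness conclusion. For between-arm results favouring the intervention, the chance at the settings shown exceeds one half only under independence, which is not credible for repeated measures on the same people.
- **The count should not be inflated.** A reader might add tests of subscales, because the HADS is described as having two dimensions. No separate subscale tests are planned in the text, so none are counted.

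**Conclusion.** The concern holds in this form: the article fixes an unadjusted 0.05 rule for all tests, plans between-arm comparisons of ten outcomes at four times, and identifies none of them as the basis for the effectiveness conclusion or for the sample size.

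Under no true effect, the risk of some false significant arm difference is roughly 60–87% over 40 comparisons. The risk of one that favours the intervention is roughly 31–64%. At the extreme correlations the two figures are 42% and 21%. Even that 21% is about eight times the 2.5% that a single two-sided test would carry (0.21 / 0.025 = 8.4).

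The test count and the independence results follow from the document. The correlated results rest on assumed correlations and on no effect on any outcome. The size of the problem is therefore a range, but the direction does not depend on which value in that range is right.

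**What to change.** Before unblinding:

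1. Name one primary effectiveness outcome and one between-arm contrast. Patient EQ-5D-5L is a candidate, since health-related quality of life comes first in the hypotheses and in Table 3. The contrast could be at one chosen time or averaged over T1–T4. The choice is for the trial team; what matters is that it is single and fixed in advance.
2. Attach the sample-size statement to that contrast.
3. Replace the closing sentence on p-values with wording such as: a two-sided level of 0.05 applies to the primary contrast only; all other outcomes, times and within-arm comparisons are secondary and are reported as estimates with 95% confidence intervals; any of them that will be called significant is adjusted for multiplicity, for example by Holm's method.

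This returns the error rate of the primary claim to 5% two-sided. It is a change of wording and needs no new data. The downside is that fewer secondary results may be called significant.

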## Discussion

This study aims to evaluate the acceptability, feasibility, effectiveness and cost-effectiveness of early palliative care interventions in older European persons with complex chronic conditions. This is done using a randomised controlled trial design in four European cities: Valencia (Spain), Amadora (Portugal), Thessaloniki (Greece) and Highlands (UK). In accordance with the local clinical pathways and resources, individualized care pathways will be designed for each city. Carrying out individualized care pathways will foster that the InAdvance interventions are feasible and sustainable beyond the project life. This could also help facilitate future implementation into different key care levels: hospice care, primary care and community and social care. The development of early palliative care intervention was based on the experiences and preferences of a diverse group of stakeholders (older persons, informal caregivers/relatives and healthcare professionals), and was oriented by the end-users which could generate an adequate compliance to the intervention [42].

This study has several strengths. As far as we know, this is one of the first European studies that aims to integrate early palliative care in the daily clinical routine specifically addressing on patients with non-oncological complex chronic conditions in different European settings. Studying the feasibility of early palliative interventions is relevant, specially due to the stigma associated with palliative care or with end- of- life care. An early integration of palliative care among oncological patients has been proved feasible and well-accepted both for patients and their relatives [43]. Additionally, according to a recent policy brief from the European Observatory on Health Systems and Policies [44], a skilled assessment of patients’ needs and the support from them and their relatives can improve the experiences for both and may reduce costs of care. In this line, InAdvance intervention aims to timely detect palliative needs and to assist them in accordance with patients’ and their relatives’ goals and desires. In addition, a set of technology-based secondary interventions will also be deployed as a manner of feasibility/proof-of-concept studies. These technologies would also be a relevant asset in the support, monitoring and palliation of physical, emotional and social needs of older patients [45] as well as an effective learning method for healthcare professionals [46].

The proposed study has some limitations and we expect to encounter some challenges. There is an absence of a uniform definition on early palliative care in Europe. No complete agreement has been reached about which model of care and interventions should be early integrated in the course of chronic conditions with the aim to improve the quality of life of patients and their families [47, 48]. The approaches and interventions implemented differ widely depending on the diseases considered, the care settings, the outcome measures and the geographic, social and cultural contexts of both patients and medical systems [49, 50]. The InAdvance interventions will be developed based on specific core elements of palliative care, taking into consideration various stakeholders’ perceptions, services and resources available for the palliative care and local culture and legal framework. The InAdvance aims to provide insights into the key components that could foster the timely integration of palliative care in the trajectory of severe chronic conditions. Participation of older persons with complex chronic conditions may be a challenge, especially during the COVID-19 pandemic. To increase participation, remote recruitment, enrollment, visits and data collection procedures, such as phone or videoconference calls will be considered increasing the efficiency, reducing costs and mitigating the risk of infection especially among older populations with chronic conditions [51].

As the growth of the older population will pose a challenge for the healthcare system, providing more effective care is necessary. A patient-centred and early implementation of palliative care may adequately address the needs of patients with chronic conditions. The InAdvance project will further elucidate whether such an approach could be effective and feasible for older population in different settings and identify potential effective elements of early palliative care, with the aim to define mechanisms for establishing a supportive ecosystem for palliative care.

